## 8.5 Definition of Study Endpoints

#### Complete remission rate (CR rate):

Proportion of patients who achieve a complete remission (CR, as defined above) at any time point during study participation.

#### Overall response rate (ORR):

Proportion of patients who achieve either a complete remission (CR), a CRp or a CRi, as defined above, at any time point during study participation.

#### Overall survival (OS):

Time interval from day 1 of study treatment to the day of death. For a patient who is not known to have died by the end of follow-up, observation of OS will be censored on the date the patient was last known to be alive.

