##### **3.1.1 Benefit / risk ratio**

Patients eligible for this trial have a chance of survival with any other therapy of 25% after one year [2]. The risk of this trial is that addition of BIBF 1120 to low-dose cytarabine increases treatment-related death due to extensive toxicity. Since a MTD for BIBF 1120 monotherapy and for combination therapy with various cytotoxic agent has already been evaluated in clinical trials in solid tumors, it seems justified to perform an enhance dose finding for the combination therapy of BIBF 1120 and low-dose cytarabine.

The possible benefit of the trial is to decrease the rate of treatment failure in the trial population. For a single patient, this could result in increased life-span, ideally without evidence of leukemia. Given the extensively high rate of primary or secondary treatment failure in this patient population, the medical need for novel, rational therapeutic approaches for this patient population is overwhelming. As pointed out above, the molecular rationale for

the therapeutic administration of BIBF 1120 in AML is well founded. Thus, the benefit/risk ratio for a patient to participate in this trial appears favorable.

Since the application of 5-azacytidine has a proven efficacy in low-proliferating AML with  $\leq 30\%$  bone marrow blasts [17], AML patients with  $\leq 30\%$  bone marrow blasts should be treated with 5-azacytidine if possible. Accordingly, patients qualifying for an intensive treatment have a chance of achieving a complete remission of 50% and should therefore be treated with an intensive approach. However, no therapeutic approach exists in patients with  $>30\%$  bone marrow blasts and adverse cytogenetic risk unfit for an intensive treatment, and these patients have the highest need for therapy improvement. Patients with non-adverse cytogenetic risk and not qualifying for both therapy with 5-azacytidine and intensive chemotherapy only have an 18% chance of achieving a complete remission upon treatment with low-dose cytarabine alone. It therefore seems justifiable to include these patients (with AML not qualifying for both 5-azacytidine and intensive chemotherapy) into this trial.

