### 3.2.2 Phase II

Primary endpoint:

- to evaluate the overall response rate (ORR, consisting of: CR, CRp and CRi as defined by IWG criteria) of the whole study population

Secondary endpoints:

- to compare the ORR rate of the Flt3-mutated patients versus the Flt3-wildtype patients and within different cytogenetic risk groups
- to evaluate the CR rate of the whole study population
- to compare the CR rate of the Flt3-mutated patients versus the Flt3-wildtype patients and within different cytogenetic risk groups
- to evaluate the one-year overall survival (OS) of the whole study population

---

 response criteria by the International Working Group (IWG) are defined as:

- Complete remission (CR): less than 5% bone marrow blasts and regeneration of both peripheral neutrophils to  $>1,000/\mu\text{l}$  and platelets to  $>100,000/\mu\text{l}$
- Complete remission with incomplete platelet recovery (CRp): less than 5% bone marrow blasts and regeneration of peripheral neutrophils to  $>1,000/\mu\text{l}$  with a platelet count of  $<100,000/\mu\text{l}$
- Complete remission with incomplete neutrophil recovery (CRi): less than 5% bone marrow blasts with a neutrophil count of  $<1,000/\mu\text{l}$  with or without platelet recovery

- to compare the one-year overall survival (OS) of the Flt3-mutated patients versus the Flt3-wildtype patients and within different cytogenetic risk groups
- to evaluate the relapse-free survival (RFS) of the responding patients
- to evaluate the time to response (CR, CRp or CRi) of the responding patients
- to evaluate the toxicity in the whole study population
- to evaluate the development of biomarkers indicating the course of disease, including genetic, epigenetic, transcriptional, protein and phosphoprotein markers in leukemic blasts, bone marrow, peripheral blood cells, serum and plasma, and bone marrow microvessel density.

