#### **6.1.5 Evaluations during follow-up in relapsed / refractory patients**

- In patients with relapse or patients refractory to treatment after up to 6 cycles, patients will be monitored for new AEs / SAEs until 28 days after the last protocol treatment and for outcome of any AEs / SAEs (see chapter 7).
- Patient's survival status will be monitored until one year after start of treatment.
- Additional follow-up visits will be performed at the investigator's discretion

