### 6.4 Duration of the study

|                         |                                                  |
|-------------------------|--------------------------------------------------|
| Accrual time: 24 months | Treatment / observation a : 12 months |
|-------------------------|--------------------------------------------------|

a In case of a relapse / treatment failure, a study exclusion or a refusal of informed consent, patients will be followed up for survival until one year after the start of the first induction cycle.

Assuming an accrual time of 24 months and a duration of treatment, observation or follow-up (of the last included patient) of approximately 12 months the duration of the study will be approximately 36 months.

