#### **Protocol-specific clarifications to this definition:**

Therapy-related cytopenias as signs of an intended antileukemic activity are by definition no adverse events. However, complications of such cytopenias (i.e. neutropenic infection, thrombocytopenic bleeding) do constitute an AE.

In order to monitor the safety of the trial participants throughout the trial, untoward medical occurrences between signature of the informed consent form and first administration of the investigational medicinal product also have to be documented as adverse events.

A pathological finding, improved or unchanged in comparison to baseline, does not constitute an adverse event.

Symptoms of the disease under study should not be classified as AEs as long as they are within the normal day-to-day fluctuation. Worsening of the underlying disease or other pre-existing conditions will be recorded as an AE.

Abnormal laboratory values without therapeutic consequences do not have to be documented on the AE form. Instead, they will be documented on the laboratory values form in the CRF only.

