### 8.2 Statistical Analysis Plan

The Statistical Analysis Plan (SAP) will be established without having insight into study data. In the SAP the statistical analyses are described in detail. The primary analysis will be performed using the one-sample (exact) Binomial test, applied according to the intention to treat principle (ITT). This means that every patient included into the study will be evaluated, even if he or she did not receive study medication, or any other violations of the study protocol occurred. Results of primary ITT analyses provide confirmatory statistical evidence. In addition to the ITT analysis a per protocol analysis (PP) will be performed. In the PP analysis only those patients are included who could be treated with full adherence to the protocol. Beyond the primary analysis, pre-specified analyses of secondary endpoints will be performed with appropriate  $\alpha$ -adjustment due to multiplicity. Further exploratory analyses will be performed and interpreted according to the relatively low level of scientific evidence provided.

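### Overall survival and its follow-up are timed from day 1 of treatment, so included patients who never start have no OS time, although one-year OS is set for the whole study population

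*Protocol*

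**What the plan says.** - **Time origin.** Section 8.5 defines OS as "Time interval from day 1 of study treatment to the day of death". For patients not known to have died, "observation of OS will be censored on the date the patient was last known to be alive". No origin is given for a patient without a day 1.
- **Population for OS.** The phase II secondary objectives in 3.2.2 include "to evaluate the one-year overall survival (OS) of the whole study population".
- **Who counts as included.** For the primary analysis, 8.2 states that "every patient included into the study will be evaluated, even if he or she did not receive study medication".
- **Survival follow-up.** In 6.1.5, "survival status will be monitored until one year after start of treatment". In the footnote to 6.4, "patients will be followed up for survival until one year after the start of the first induction cycle"; that footnote also covers patients excluded from the study or refusing consent. Sections 5.4.3 and 6.1.4 likewise stop at one year after therapy begins.
- **Interval before treatment.** Section 7.1.1 recognises one: "untoward medical occurrences between signature of the informed consent form and first administration of the investigational medicinal product also have to be documented". Its length is not fixed.

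**The concern.** These provisions cannot all be applied to a patient who is registered and then never treated. That patient belongs to the study population but has no date from which survival can be measured and no date to which vital status must be followed. If the text is followed literally, the patient disappears from the OS analysis.

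The gap matters most for deaths between registration and the first dose. In patients aged 60 or over who are unfit for intensive therapy, such deaths are plausible. They are the earliest failures, and they would not count in a one-year OS labelled as that of the whole population. The response rate and OS would then rest on different denominators without the report saying so. If vital status is never collected for these patients, a later analysis plan may not be able to recover it.

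**Working it through.** **The plan's own figures.** Section 8.1 gives 111 evaluable plus 11 not evaluable, 111 + 11 = 122 recruited. There is no sample size, event count, hypothesis or power for OS, so there is no OS figure to reproduce. I use 122 as the denominator.

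**The text applied to one patient who is included and never treated.**

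| Provision | Result |
|---|---|
| 3.2.2, population for one-year OS | belongs to the study population |
| 8.2, primary response analysis | evaluated |
| 8.5, start of OS | undefined |
| 8.5, censoring date | defined, but no start to measure from |
| 5.4.3, 6.1.5, 6.4, end of survival follow-up | undefined |

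**Effect of counting pre-treatment deaths.** Let S be one-year OS from day 1 in treated patients and k the number who die before day 1. Over all 122 patients,

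OS = S × (122 − k)/122.

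The protocol gives neither S for this trial nor k. I assume S = 25%, the background figure in 3.1.1, and k from 0 to 11. The upper limit borrows the allowance of 11 in 8.1, which is meant for missing primary data and serves here only as a bound.

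- k = 0: 25.0%
- k = 4: 0.25 × 118/122 = 24.2%, a fall of 0.8 points
- k = 11: 0.25 × 111/122 = 22.7%, a fall of 2.3 points

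With an assumed S of 35%, k = 11 gives 0.35 × 111/122 = 31.8%, a fall of 3.2 points.

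**Effect of the earlier origin.** If the clock starts at registration, g days before day 1, a treated patient's one-year mark falls at day 365 − g of treatment. Under a constant hazard (an assumption), S becomes 0.25^((365 − g)/365):

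- g = 7: 0.25^(358/365) = 25.7%
- g = 14: 0.25^(351/365) = 26.4%

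**Both effects together**, as one-year OS from registration over all 122:

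| k | g = 0 | g = 7 | g = 14 |
|---|---|---|---|
| 0 | 25.0% | 25.7% | 26.4% |
| 4 | 24.2% | 24.8% | 25.5% |
| 11 | 22.7% | 23.4% | 24.0% |

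The two effects cancel where 122 − k = 122 × 0.25/S(g): at about k = 3.2 for a 7-day gap and k = 6.3 for a 14-day gap. The gaps are assumptions. Section 6.2 allows most baseline evaluations up to 14 days before treatment but requires blood count and chemistry within 4 days, and the time from registration to treatment is not stated.

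**Scale.** The standard error of a 25% proportion in 122 patients is √(0.25 × 0.75/122) = 3.9 points, larger than any shift from 25% in the table.

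**The case against.** Starting OS at the first dose is a legitimate choice in a single-arm trial, where there is no randomisation date to preserve. The sentence in 8.2 about untreated patients explains intention to treat for the primary response test and is not stated for OS. The phrase about the whole study population in 3.2.2 contrasts with the Flt3 and cytogenetic subgroups beside it; the same list applies it to toxicity, which presupposes treatment. On that view one clause naming treated patients as the OS population would be enough, and the SAP could supply it.

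Much of this stands. The 8.2 sentence does not govern OS, and a first-dose origin would be acceptable if OS were declared for treated patients. The protocol makes no such declaration, and 3.2.2 points the other way on its ordinary reading. Nor is the matter simply left to the SAP: the protocol itself fixes the origin and the follow-up window, and an analysis plan cannot recover vital status that was not collected.

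A reader might also infer more than the documents support:

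- **That the day-1 definition always flatters OS.** It does not. The difference vanishes if everyone starts at once, and the earlier origin can outweigh the added deaths. Patients who do not start for other reasons, such as refusal, may also be alive at one year.
- **That OS is formally tested against 25%.** Section 3.1.1 says "Patients eligible for this trial have a chance of survival with any other therapy of 25% after one year", but as benefit/risk background. No OS threshold or test is stated.
- **That the registration date is already on record.** The items listed in 4.3.1 do not include it, although a date will exist when the number is assigned.

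**Conclusion.** The inconsistency is in the current text. As written, OS covers only patients who start treatment, while the objective names the whole study population and the primary response analysis covers every included patient. Patients who never start have no OS time and no defined survival follow-up.

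The numerical effect is probably small. Taken alone, counting pre-treatment deaths lowers one-year OS by 0 to 2.3 points, given 25% in treated patients and 0 to 11 such deaths among 122. All of these inputs are assumptions, because the protocol gives no number of untreated patients. Once the shift of the clock is included, the direction of the net change is uncertain. The case therefore rests on an undeclared population and on vital status that may be lost, and not on a demonstrated bias. It is a minor-to-moderate point on a secondary endpoint.

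**What to change.** 1. In 8.5, define OS from the date of registration for every patient included in phase II.
2. Add the registration date to the CRF.
3. Align 5.4.3, 6.1.4, 6.1.5 and 6.4 so that vital status is followed to one year from registration for all included patients, treated or not.
4. Keep OS from day 1 in treated patients as a supportive analysis, labelled as such.

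The cost is a few sentences, one CRF field and vital-status checks on what are probably few untreated patients. The reported one-year OS may differ slightly, in either direction. The change should be made before follow-up of these patients is lost.

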#### Relapse-free survival (RFS):

Time interval from the first day a leukemia-free state is achieved in patients who achieve a CR / CRi / CRp until relapse or death from any cause, whatever occurs first. For a patient who is not known to have died or have relapsed by the end of follow-up, observation of RFS will be censored on the date the patient was last known to be alive and in CR.

## 9 QUALITY ASSURANCE

### 9.1 Data Monitoring Committee

The DMC will monitor the safety of the study. During phase I, the DMC members will receive safety reports after completion of each dose level. In addition, the DMC decides on the recommended dose for phase II before start of phase II of the study. During the phase II part of the study, the DMC members will receive safety reports every 3 months. After receipt of each safety report the DMC can recommend about continuation, modification, or termination of the study. For details of the DMC and mode of action, see attachment K (DMC charta).

### 9.2 Reference Laboratories

#### 9.2.1 Reference diagnostics for cytomorphology

As stated above, a central review of selected cases will be performed in one of the three diagnostic reference centers.

|                                                                                                                                                                                                                                                                                                                               |                                                                                                                                                                                                                                                                                                                                     |                                                                                                                                                                                                                                                                                            |
|-------------------------------------------------------------------------------------------------------------------------------------------------------------------------------------------------------------------------------------------------------------------------------------------------------------------------------|-------------------------------------------------------------------------------------------------------------------------------------------------------------------------------------------------------------------------------------------------------------------------------------------------------------------------------------|--------------------------------------------------------------------------------------------------------------------------------------------------------------------------------------------------------------------------------------------------------------------------------------------|

### 9.3 Monitoring

Before the beginning of the study there will be a central meeting for all investigators from all participating centers (initiation meeting). At this meeting there will be a central training concerning all the relevant details of the study.

During the phase I part of the study, 100% of the patients will be monitored.

During the course of the study each participating center will be visited for monitoring one to four times. During each of these visits, source data verification will be performed on the basis of a pre-specified sampling plan. The ZKS Muenster will generate this plan. Furthermore, at these visits problematic cases as specified by the coordinating investigator will be discussed. Study centers can be selected for additional monitoring visits during the course of the study as judged necessary.

At the end of the study there may be a special close out visit for each center.

#### 9.4 Direct access to source data - documents

The investigator / institution will permit trial-related monitoring, audits, IRB / IEC review and regulatory inspection, providing direct access to all related source data / documents. CRFs and all source documents, including progress notes and copies of laboratory and medical test results must be available at all times for review by the sponsor's clinical trial monitor, auditor and inspection by health authorities.

#### 9.5 Data Management

For data management, an electronic database will be generated at the ZKS Muenster. The database will be equipped with an audit trail that allows for a full follow-up of the history of each item.

Data capture of the study is paper based using pre-specified case report forms (CRF). The CRF will be completed and sent to the study office within two weeks (Phase I) and within four weeks (Phase II). At the study office, the incoming CRFs will be assessed for plausibility and forwarded to the ZKS. The ZKS will try to resolve possible implausibility by queries to the responsible investigator at the involved center. The investigator has to respond by a signed written statement to be sent to the study office.

Further data processing including data entry and biometrical analysis will be done at the Institute of Biostatistics and Clinical Research of the university hospital of Münster (IBCR) and at the ZKS. This will be done in close cooperation with the coordinating investigator.

## **10 INVESTIGATOR'S RESPONSIBILITIES, ETHICAL CONSIDERATIONS, CONFIDENTIALITY, PUBLICATION AND INSURANCE**

### **10.1 Investigator's responsibilities**

The Coordinating Investigator has more than two years experience in the conduct of clinical trials.

#### **10.1.1 Declaration of Helsinki and GCP compliance**

The Investigator undertakes to perform the study in accordance with the Declaration of Helsinki (in its latest version Seoul, 2008) and the ICH Guidelines in Good Clinical Practice as well as with the applicable regulatory requirements.

#### **10.1.2 Protocol adherence**

The Investigator must adhere to the protocol as detailed in this document. The Investigator will be responsible for enrolling only those patients who have met protocol eligibility criteria.

#### **10.1.3 Documentation and retention of records**

##### **10.1.3.1 Case Report Forms (CRFs)**

The Investigator is responsible for maintaining adequate and accurate CRFs which have been designed to record all observations and other data pertinent to the clinical investigation. CRFs should be filled out completely by the Investigator or delegate as stated in the Site Delegation List. All CRFs should be completed in a neat, legible manner to ensure accurate interpretation of the data; a black ball-point pen should be used to ensure the clarity of reproduced copies of all CRFs. Corrections should be made by lining out the entry to be corrected by a single line and dating and signing the corrected entry. CRFs should be completed and sent to the ZKS within 6 weeks.

As described in the ICH GCP Guidelines (E6), 'essential documents', including CRFs, source documents, consent forms, laboratory test results, and medication inventory records, will be archived by the Investigator according to the current rules and regulations.

##### **10.1.3.2 Recording, access, and retention of Source Data**

Source documents are defined as any document where the information is collected during the study procedures for a specific subject. Source documents can be patient's medical file, appointment books, original laboratory reports, X-rays, Investigator or nurses notes, etc.

Source data to be collected during this study will include, but is not restricted to: patient's medical file, original laboratory reports, histology, and pathology reports.

